#### (c) Complications

The complication rate in this patient category is rather high, but heterogeneous. The rate of thrombo-embolic complications may depend on the type of intervention (cemented vs. non-cemented).

However, the incidence of deep vein thrombosis (DVT) and pulmonary embolism (PE) is such that an unachievable high number of patients is needed to acquire adequate power.

In conclusion, the total number of patients per group a set on 100, making a total of 200 patients is needed for this study.

### Statistical analysis

#### Primary outcome measures

The differences in operation time, mid-thigh pain, complications and TUG test will be analyzed using a Student's t-test, setting the level of significance at *p *< 0.05.

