## Abstract

**Background:**

A discussion is ongoing whether displaced femoral neck fractures in elderly patients should be treated with a non-cemented or a cemented hemiarthroplasty. A recent Cochrane analysis stresses the importance of further research into the relative merits of these techniques. We hypothesise that non-cemented hemiarthroplasty will result in at least the same technical-functional outcome and complication rate, with a shorter operation time.

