#### (b) Functional outcome

Only for patients who are admitted from their own homes or assisted living facilities, functional outcome is measured by the Timed-Up-and-Go (TUG) score and the Groningen Activity Restriction Scale, and mid-thigh pain a non-inferiority design is used. [10,14]

• TUG performed; Giving the fact that at discharge with a cut-off point of over 30 seconds is significantly associated with falls. Less than 24 seconds is considered good functioning and has hardly any chance to fall. 42 seconds is considered poor functioning with a considerable chance to fall. [14] About 30% of the patients have a poor score at discharge. About 70% of all patients are admitted from their own homes or assisted living facilities. If non-inferiority is considered for TUG, a worsening of score from 30 to 42 is considered clinically relevant, with a SD of 10 sec., giving 16 patients a group. Corrected for the percentage admitted from home or assisted living facility (70%) and the drop out of 35% gives 34 patients a group

• GARS: The GARS data for this group of patients are insufficient to make valid calculations of statistical power. While data for multiple sclerosis patients and healthy older patients are available, there are none for patients with a hip fracture. An estimate is made based on preliminary data from a prospective survey in progress. As soon as sufficient data from this survey are available a final power calculation for GARS will be done.

• Mid thigh pain

Rather varying figures about mid-tight pain are reported in literature. D'Lima [5] reported 40 vs. 3% whereas v/d Wal et al. [15] reported 20 vs. 12% in non-tight proximal fit prosthesis. Therefore the average values of these two studies are taken.

π1 = 30%, π 2 = 7.5%, π = (30%+7.5%)/2 = 18.75%

n_1 _= n_2 _≥ 21* (0,1875*(1-0,1875))/(0,225)^2 ^= 63.2.

If the 25% 1-year mortality combined with expected 10% lost-to follow-up (or missing values) is taken into account this number is raised by 35%, then a total of 86 patients a group is needed. [16]

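### The analysis section tests TUG, mid-thigh pain and complications for a difference without a margin, which cannot establish the no-worse hypothesis; only operation time is matched to its test

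*Protocol article*

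**What the plan says.** **Hypothesis** (Abstract, Background; repeated in the Discussion): "non-cemented hemiarthroplasty will result in at least the same technical-functional outcome and complication rate, with a shorter operation time". Function and complications are therefore no-worse questions, and operation time is a superiority question.

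**Design** (Determination of sample size, (b) Functional outcome): the opening sentence covers TUG, GARS and pain and ends "mid-thigh pain a non-inferiority design is used". For TUG the section adds "a worsening of score from 30 to 42 is considered clinically relevant, with a SD of 10 sec., giving 16 patients a group", which implies a margin of 42 − 30 = 12 s. For mid-thigh pain it gives two expected rates, "π1 = 30%, π 2 = 7.5%, π = (30%+7.5%)/2 = 18.75"%, and no margin.

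**Complications** (Determination of sample size, (c) Complications): no margin and no sample size. For thrombo-embolic events the section concedes that "an unachievable high number of patients is needed to acquire adequate power".

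**Analysis** (Statistical analysis, Primary outcome measures): "The differences in operation time, mid-thigh pain, complications and TUG test will be analyzed using a Student's t-test". The threshold for all four outcomes is p < 0.05. No margin, confidence-limit criterion or sidedness is given.

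**The concern.** A t-test of a difference asks whether the data are compatible with zero difference. A no-worse claim asks whether the data exclude a deficit as large as a stated margin. The two can disagree both ways: a non-significant result may leave a large deficit open, and a significant result may reflect a difference well inside the margin.

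The analysis section gives one test for four primary outcomes, and that test matches the hypothesis for only one of them. At stake is what the trial may conclude on function, pain and complications. Where the evaluable numbers are modest, a non-significant p-value says little, and the plan supplies no other criterion by which to judge the hypothesis.

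**Working it through.** **1. The plan's own figures.** The factor 21 in the pain formula is 2 × (1.960 + 1.282)² = 21.01, that is, two-sided 5% and 90% power.
- TUG, Δ = 12 s, SD = 10 s: n = 21.01 × 10² / 12² = 14.6, so 15 per group by the normal approximation and 16 by the exact t calculation. The stated 16 is reproduced. A non-inferiority calculation with margin 12 s, one-sided 2.5% and no true difference gives the same 15.
- TUG after inflation: 16 / 0.70 / (0.75 × 0.90) = 33.9, or 16 / 0.70 / 0.65 = 35.2, against the stated 34.
- Pain: 21 × 0.1875 × 0.8125 / 0.225² = 63.2, as stated; × 1.35 = 85.3, rounded up to 86. This is a formula for detecting a difference. The 22.5 points are an expected difference, not a margin.

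**2. Evaluable numbers at 100 per group, from the plan's rates.** TUG: 100 × 0.70 × 0.65 = 45.5, taken as 45. Pain: 100 × 0.65 = 65. Complications: 100, deliberately without attrition.

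**3. TUG.** SE = 10 × √(2/45) = 2.108 s.
- True deficit 12 s: 12 / 2.108 = 5.69. The chance of a non-significant result is Φ(1.96 − 5.69) = Φ(−3.73), about 0.01%.
- True deficit 5 s, inside the margin: 5 / 2.108 = 2.37, so the chance of significance is Φ(2.37 − 1.96) = 66% by the normal approximation and 65% by the exact t calculation.
- Non-inferiority against 12 s, no true difference, one-sided 2.5%: power = Φ(5.69 − 1.96) = Φ(3.73) > 0.999.

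**4. Mid-thigh pain as a yes/no outcome, as in the sample-size section.** The 20% vs 12% are one of the two sets of cited rates in section (b). With 65 per group:
- SE under the null = √(2 × 0.16 × 0.84 / 65) = 0.0643; SE under the alternative = √((0.20 × 0.80 + 0.12 × 0.88) / 65) = 0.0639.
- Power = Φ((0.08 − 1.96 × 0.0643) / 0.0639) = Φ(−0.72) = 24%, so 76% non-significant. With 45 per group (if pain is also restricted to the 70% admitted from home or assisted living), 82%.
- At the planning rates of 30% vs 7.5% with 65 per group, power is about 92%.

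**5. Complications, 30% vs 20% (assumed; the protocol gives no rates), 100 per group.**
- SE under the null = √(2 × 0.25 × 0.75 / 100) = 0.0612; under the alternative = √((0.21 + 0.16) / 100) = 0.0608.
- Power = Φ((0.10 − 1.96 × 0.0612) / 0.0608) = Φ(−0.33) = 37%, so 63% non-significant. At an assumed 40% vs 30% it is 68%. Attrition would raise both.
- 95% CI half-width for the *difference* between two rates near 30%: 1.96 × √(2 × 0.3 × 0.7 / 100) = 12.7 points. (For a single rate it is 1.96 × √(0.3 × 0.7 / 100) = 9.0 points.)

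**6. Would a non-inferiority test of pain be powered?** Assume equal true rates p between 7.5% and 18.75%, one-sided 2.5% and 90% power: n = 21.01 × p(1 − p) / margin².

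| Margin (assumed) | Evaluable per group | Randomised per group (÷ 0.65) |
|---|---|---|
| 10 points | 146 to 321 | 225 to 494 |
| 15 points | 65 to 143 | 100 to 220 |
| 22.5 points | 29 to 64 | 45 to 99 |

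With 100 per group, a 10-point margin is out of reach and a 15-point margin is met only at the lowest rate.

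**The case against.** The strongest reply is that the analysis section is one sentence in a condensed article. It states neither sidedness nor the null value, a t-test can be run against a shifted null, and confidence-limit mechanics often sit in an analysis plan that is not shown. This stands in part: no fault lies in leaving mechanics out. But the article does name a test of differences and a significance level for all four outcomes together, and carries over no margin. For pain and complications there is no margin anywhere in it to carry over.

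Three further points are fair and limit the finding:
- The no-worse statements do not all cover the same outcomes. The hypothesis names function and complications, not mid-thigh pain; section (b) covers function and pain, not complications; and the TUG bullet is worded conditionally. The unconditional opening of section (b) and the hypothesis itself still stand.
- For pain, a difference test agrees with the way pain was sized. The conflict there lies inside section (b), between the non-inferiority label and the difference formula.
- The pain and complication figures above are for a two-proportion test, an approximation to a t-test on yes/no data.

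Some stronger readings are tempting. A reader might infer that the investigators will take p ≥ 0.05 as proof of equality; the protocol never says so. A reader might infer that the trial cannot answer its main question; yet operation time is tested suitably, and the TUG data can support the 12 s comparison. A reader might count a TUG worsening of a few seconds as a missed harm; section (b) places clinical relevance at 12 s, and a deficit of that size would almost never be missed.

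**Conclusion.** The contradiction is in the text. For TUG, pain and complications, the test named in the analysis section cannot support a conclusion of no worse; for operation time it is appropriate.

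The consequence differs by outcome. For TUG it is a missing decision rule more than a risk of missing a relevant deficit, and differences inside the margin may be significant without contradicting non-inferiority. For pain and complications, a non-significant result is likely even when the non-cemented arm is worse by 8 to 10 points, so it would carry little information.

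This rests on the protocol's attrition and admission rates, its SD of 10 s and its cited pain rates. The complication rates are assumptions. Whether 12 s is a suitable margin is not judged here; it is simply the only one the document implies.

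**What to change.** In Statistical analysis, Primary outcome measures:
- **Operation time:** keep the superiority t-test.
- **TUG:** report non-cemented minus cemented with a two-sided 95% CI, and conclude non-inferiority only if the upper limit is below the 12 s of section (b).
- **Mid-thigh pain:** reconcile section (b) by dropping the non-inferiority label, in line with the difference formula used, and report the difference in proportions with its 95% CI. If the label were kept, a margin would have to be stated and justified, and a tight one would need more than 100 per group.
- **Complications:** report the risk difference with its 95% CI, make no claim of being no worse, and align the hypothesis in the Abstract and the Discussion accordingly.
- **Interpretation:** state that p ≥ 0.05 is not evidence of equality.

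The cost is rewording, with no added patients or data. The downside is that the claims for pain and complications become weaker.

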#### Secondary outcome measures

We will use the chi-squared test or Fisher's exact test for the binary variables. In cases of paired binary data (outcome variables) we will use the McNemar test and a paired t-test for mean differences. In the case of a statistically significant association (*p *< 0.05), we will use a logistic regression to model the probability/odds of an outcome.

The variables obtained from the clinical evaluation will be tabulated and analysed as mean, standard deviation, minimum and maximum values. All analyses will be performed using SPSS software (SPSS Inc., Chicago, IL, USA).

Kaplan Meijer survival analysis will be done after final follow up, using failure (reoperation) and mortality as endpoints.

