### Study variables

Preoperatively, social demographic data, the ASA classification, Groningen Activity Restriction Scale (GARS, from which the Parker mobility score can be derived) and the SF-12 are obtained from each patient. [10,12,13]

The main outcome measures of this study are the functional results, complication rate and duration of surgery of the hemiarthroplasty.

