### Primary outcome measures

• Duration of surgery is defined as skin-to-skin surgical time, measured in minutes.

• Complications, divided in major and minor complications, are recorded during the follow up period of 1 year. The complications are ranked in the modified Elixhauser mode, as described by Parvizi.[11]

• Functional outcome is measured by the Timed-Up-and-Go (TUG) score and the Groningen Activity Restriction Scale (GARS). [10,14]

• Postoperative mid-thigh pain is defined as pain explicit in the front and mid part of the femur, and scored on a 4-point ordinal scale (non/mild/moderate/severe).

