### Secondary outcome measures

Living conditions at final follow up are measured in percentage of pre-fracture situation.

• Self reported health-related quality of life is measured by the SF 12. [13]

• Standard radiological evaluation of hemiarthroplasty and cement positioning and adequate size of the hemiarthroplasty measured on plain AP and axial X-rays of the operated hip. Adequate AP positioning is defined as less than 10 degrees varus or valgus. Adequate axial positioning is defined as 0–15 degrees anteversion.

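### For SF-12 the plan names only a within-patient test of means, so no test compares cemented with non-cemented, and logistic regression is run only after p < 0.05

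*Protocol article*

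**What the plan says.** All references are to the Protocol article.

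- **Statistical analysis, Secondary outcome measures.** Three commitments matter here. For binary variables: "We will use the chi-squared test or Fisher's exact test for the binary variables". For paired data: "In cases of paired binary data (outcome variables) we will use the McNemar test and a paired t-test for mean differences". Then a conditional step: "In the case of a statistically significant association" at p < 0.05, "we will use a logistic regression to model the probability/odds of an outcome". No covariates are named for that model. Kaplan-Meier analyses of reoperation and mortality are also planned.
- **Statistical analysis, Primary outcome measures.** Operation time, mid-thigh pain, complications and TUG are compared by Student's t-test at p < 0.05. GARS is not in that list.
- **Secondary outcome measures (outcome definitions).** "Self reported health-related quality of life is measured by the SF 12".
- **Primary outcome measures (outcome definitions).** Functional outcome is TUG and GARS, so GARS is primary.
- **Study variables.** Among the preoperative data: "Groningen Activity Restriction Scale (GARS, from which the Parker mobility score can be derived) and the SF-12 are obtained from each patient". No preoperative TUG is listed.
- **Study design and Discussion.** There are two randomised groups of 100, and the stated purpose is to compare the two types of prosthesis.

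**The concern.** McNemar and paired t-tests need pairs. No matching of patients across arms is described, so a pair can only be the same patient at two times. These tests then answer whether patients changed, which is not the question the trial was randomised to answer. For SF-12 no other test of means is named under its heading.

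If paired results were read arm by arm, a significant change in one arm and a non-significant one in the other could pass for a treatment difference. If the arms were pooled, the result would say nothing about the prostheses.

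The regression rule raises a separate problem. When a model is fitted only after significance, the reported odds ratios come from a sample selected for being large.

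Preoperative SF-12 and GARS are collected, yet the only stated analysis that could use the SF-12 baseline is the within-patient one, and none is stated for GARS.

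**Working it through.** No figure in the plan rests on these test choices, so there is none to reproduce. The check is to match outcomes to named tests, then illustrate the consequences.

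**1. Which outcomes have a named test that can compare the arms**

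| Outcome | Role | Test named | Can it compare arms? |
|---|---|---|---|
| Operation time, mid-thigh pain, complications, TUG | Primary | Student's t-test | Yes |
| GARS | Primary | None | Not stated |
| Binary secondary variables | Secondary | Chi-squared or Fisher's exact | Yes |
| Paired binary data | Secondary | McNemar | No, change over time |
| SF-12 (score) | Secondary | Paired t-test | No, change over time |

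The gap in the secondary section is therefore the continuous outcome, SF-12.

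**2. Inputs for the illustrations**

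- From the plan: 100 per arm, 25% one-year mortality and 10% loss, so 100 × (1 − 0.35) = 65 evaluable per arm; significance level 0.05, taken as two-sided because sidedness is not stated.
- Assumed: effect sizes, the control event rate and the baseline-outcome correlation r. The documents give none of these for SF-12 or GARS.

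**3. If paired tests were read separately by arm**

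Suppose both arms truly change by the same d (in SDs of the change). Power in one arm is p ≈ Φ(d√65 − 1.96). The chance that exactly one arm is significant is 2p(1 − p).

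| d | p | 2p(1 − p) |
|---|---|---|
| 0.20 | 0.364 | 46% |
| 0.25 | 0.522 | 50% |
| 0.30 | 0.677 | 44% |
| 0.40 | 0.897 | 19% |

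The true treatment difference is zero in every row.

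**4. Regression only after p < 0.05**

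Simulation of 200,000 trials per row, 65 per arm, assumed control rate 30%, unadjusted log odds ratio:

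| True log OR | Trials passing p < 0.05 | Mean log OR among those | Ratio to truth |
|---|---|---|---|
| 0.3 | 13% | 0.87 | 0.87/0.3 = 2.9 |
| 0.5 | 28% | 0.94 | 0.94/0.5 = 1.9 |
| 0.8 | 60% | 1.03 | 1.03/0.8 = 1.3 |

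Averaged over all trials, the estimates are close to the truth (0.30, 0.50, 0.80). The exaggeration comes from the selection alone.

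**5. Value of using the preoperative score**

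Relative to comparing follow-up values alone, ANCOVA multiplies the variance of the arm difference by 1 − r². The equivalent sample-size factor is 1/(1 − r²).

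| Assumed r | 1 − r² | 1/(1 − r²) |
|---|---|---|
| 0.4 | 0.84 | 1.19 |
| 0.5 | 0.75 | 1.33 |
| 0.6 | 0.64 | 1.56 |
| 0.7 | 0.51 | 1.96 |

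For a 0.4 SD arm difference at 65 per arm, power ≈ Φ(0.4/√(2(1 − r²)/65) − 1.96). This gives 62.6% unadjusted, 75.0% at r = 0.5 and 89.1% at r = 0.7. For GARS the sample-size section restricts functional outcome to the roughly 70% admitted from home or assisted living. That leaves 0.70 × 65 ≈ 45 per arm, and the same three figures become 47.5%, 59.1% and 75.7%.

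**The case against.** The strongest defence has four parts.

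- **The arms are compared elsewhere.** A reader might infer that paired tests replace the randomised comparison throughout. The text does not support that: chi-squared or Fisher's exact tests are named for binary variables, and four primary outcomes get a two-sample t-test. This part stands and confines the point.
- **The paired tests may be harmless.** McNemar is proposed only for paired binary data, where it is the right test for change over time. The article never says the tests will be run by arm or used to claim a treatment difference. This also stands, so the table of one-arm-only significance shows a risk, not a planned analysis. It does not supply the missing SF-12 comparison.
- **An unseen analysis plan may supply the rest.** That is fair for covariates: an unadjusted comparison of randomised arms is valid, and leaving adjustment unstated in an article is no error. It may also explain why no GARS test is named. It does not cover what the article itself fixes, namely a paired test as the only test of means for secondary outcomes and a regression conditional on significance.
- **The gate does not block the main test.** Chi-squared or Fisher's test is run whatever its result, the logistic model is not called the main estimate, and the association is not limited to treatment arm. True, but the modelled odds ratios that get reported would still be a selected set.

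Two further inferences should be resisted. GARS is primary, so the secondary section does not assign it a paired test. And the non-inferiority outcomes (TUG, GARS, mid-thigh pain) are all primary, so the criticised wording does not affect a non-inferiority bound.

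**Conclusion.** The point holds in a limited form. As written, SF-12 has no test of cemented against non-cemented, and logistic estimates would exist only for outcomes that reached p < 0.05. Both follow from the article's own wording and need no assumption beyond the absence of matched pairs.

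The sizes are illustrative. Overstatement after the gate is about 1.3 to 2.9 times on the log odds scale, for true values of 0.8 down to 0.3, given 65 per arm and a 30% control rate. The precision available from adjustment is a variance factor of 0.84 to 0.51 for r between 0.4 and 0.7. Not adjusting costs precision and causes no bias. The gain should not be claimed for TUG, which has no listed baseline.

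The defect in the secondary section concerns a secondary outcome and the reporting of models. It deserves correction before analysis but does not undermine the t-tests named for the primary outcomes.

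**What to change.** In the secondary-outcome analysis section:

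1. State that SF-12 is compared between arms by ANCOVA, or by a mixed model over the 6-, 12- and 52-week visits, adjusted for its own preoperative value. Report the arm difference with a 95% confidence interval.
2. Keep McNemar and paired t-tests as descriptions of change over time only, with no inference about the prostheses drawn from them.
3. For binary outcomes, report the arm difference with a 95% confidence interval. Name in advance any logistic model and its covariates, and fit it whatever the unadjusted p-value.

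In the primary-outcome analysis section, name the GARS analysis in the same way, adjusted for preoperative GARS.

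The cost is analysis wording alone. No new data, visits or patients are needed, and the models can be run in the SPSS package the article already names.

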## Background

Patients with a hip fracture form a heterogeneous group with a high mortality rate, frequently troubled with multiple and severe co-morbidities. They are usually frail and elderly, with more than 30% aged ≥ 85 years. In European series, hip fracture patients have a 30-day mortality of >10%, and a 1-year mortality of 25–30%.[1] Despite the advances in surgical and anaesthetic techniques during the last 20 years there has been no decrease in mortality after surgical repair of hip fractures. [1]

The discussion about cemented or non-cemented hemiarthroplasty is similar to the discussion about cemented or cementless prostheses in primary hip arthroplasty. With respect to the latter, conflicting data are presented by the Swedish and Norwegian arthroplasty registers. [2,3] The general opinion is that cementless hip arthroplasties are more suitable for younger patients owing to the quality of their bone stock. In hemiarthroplasty for hip fracture surgery there are insufficient data from randomised trials to conclude on the superiority of either type of arthroplasty. Some authors found patients with cemented stems to have less pain and better mobility postoperatively than those with an non-cemented press fit.[4] Mid-thigh pain is frequently reported in primary cementless total hip arthroplasties. However, the reported incidence varies tremendously; D'Lima et al.[5] in a control-matched study reported 34%~vs.~3%, while Grübl et al.[6] in a non-controlled series reported only 3% for cementless primary total hip arthroplasties.

In cemented hemiarthroplasties polymethylmethacrylate bone cement is applied at the time of surgery, forming a solid bond between the prosthesis and the femoral bone; on the contrary, in cementless prosthesis the bonding between prosthesis and femur is dependent upon bony in-growth. Potential advantages of cementing are a less post-operative mid thigh pain, as the prosthesis is firmly fixed within the femur, and a reduced long-term revision rate from loosening of the prosthesis. Major side effects of cement are cardiac arrhythmias and cardio-respiratory collapse, which occasionally occur on application. These potentially fatal complications are caused either by embolism from marrow contents forced into the circulation or by a direct toxic effect of the cement. [7] Another major disadvantage of a cemented prosthesis is that revision arthroplasty will be more difficult.

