### Follow up

The primary follow up for each patient will be 1 year. The first postoperative assessment will be in a clinical setting as the patient is still in the hospital. Assessments at 6, 12 and 52 weeks postoperatively will be made in the outpatient clinic, unless the patient is not able to visit the outpatient clinic; in that case questionnaires are mailed to the patient (possibly through contact with a relative) to obtain as much data as possible.

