### Determination of sample size

#### (a) Duration of surgery

It is expected that a cemented hemiarthroplasty on average will take 12 min longer than a non-cemented hemiarthroplasty. Taking into account an estimated standard deviation of 12 min, a 1-year mortality of 25% and 10% of patients being lost to follow up or providing insufficient data we need a minimum of 46 patients per group.

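### A Kaplan-Meier curve for reoperation that censors deaths will overstate the proportion of patients reoperated, because the plan expects 25–30% to die within the year

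*Protocol article*

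**What the plan says.** The last paragraph of Statistical analysis, Secondary outcome measures, states: "Kaplan Meijer survival analysis will be done after final follow up, using failure (reoperation) and mortality as endpoints". Failure is defined in the parenthesis as reoperation alone. The text does not say how a patient who dies without reoperation enters the reoperation curve, and it does not mention competing risks or cumulative incidence.

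The Background reports for European series "a 30-day mortality of >10%, and a 1-year mortality of 25–30" per cent. The sample size section, under Duration of surgery, plans for "a 1-year mortality of 25% and 10% of patients being lost to follow up" or giving insufficient data. Under Follow up: "The primary follow up for each patient will be 1 year". No reoperation rate or timing is given anywhere in the article.

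**The concern.** A patient who has died can no longer be reoperated, so death is a competing event for reoperation. A Kaplan-Meier curve that censors at death treats the dead as if they could still be reoperated later at the same rate as the survivors. It therefore estimates the reoperation risk in a hypothetical population in which nobody dies.

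On the plan's own figures death is the main reason that reoperation goes unobserved: 25% of patients, against 10% lost or with insufficient data. A one-year failure percentage read off such a curve would be too high as a description of what happened to these patients. The Background and the Discussion also raise potentially fatal effects of cement. If mortality does differ between the arms, the overstatement differs too, and the curves may not show a real difference in the proportion reoperated.

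**Working it through.** The plan gives no figure for reoperation, so there is nothing to reproduce. The check compares the two estimands using the plan's mortality figures.

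**Inputs from the article.** One-year mortality of 25–30% and 30-day mortality above 10% (Background); 25% one-year mortality (sample size section); one year of follow-up.

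**Assumed.** The reoperation risk with deaths censored, r, is set at 5% or 10%. Reoperation timing is varied. For front-loaded mortality, 30-day mortality is set at 10% or 12%. Cause-specific hazards are independent.

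**Formulas for constant hazards over one year.** Let h = −ln(1 − r) and d = −ln(1 − mortality).

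- One minus Kaplan-Meier with deaths censored: 1 − exp(−h) = r.
- Cumulative incidence, the proportion actually reoperated: h/(h + d) × [1 − exp(−(h + d))].

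For r = 10% and mortality 25%: h = 0.1054, d = 0.2877, sum = 0.3930. Cumulative incidence = 0.1054/0.3930 × (1 − 0.675) = 8.7%, against 10% from Kaplan-Meier.

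| Assumed r | Mortality | Cumulative incidence | Absolute excess (points) | Relative excess |
|---|---|---|---|---|
| 5% | 25% | 4.35% | 0.65 | 15% |
| 5% | 30% | 4.21% | 0.79 | 19% |
| 10% | 25% | 8.71% | 1.29 | 15% |
| 10% | 30% | 8.44% | 1.56 | 19% |

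The relative excess hardly depends on r.

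**Front-loaded mortality.** The death hazard is split at day 30. With 10% dead by day 30 and 25% at one year, it is −ln(0.90)/(30/365) = 1.28 per year up to day 30 and [ln(0.90) − ln(0.75)]/(335/365) = 0.199 per year after that. With r = 5% and a constant reoperation hazard, the cumulative incidence is 4.17%, and 5/4.17 = 1.20.

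**Relative excess by timing of reoperation** (r = 5%, one-year mortality 25–30%):

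| Reoperation timing | Constant death hazard | 10–12% dead by day 30 |
|---|---|---|
| All in first 30 days | +1% | +5% to +6% |
| All in first 90 days | +4% | +10% to +13% |
| Half in first 90 days | +11% to +13% | +16% to +20% |
| Constant over the year | +15% to +19% | +20% to +25% |
| All after 6 months | +24% to +30% | +27% to +34% |

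**Between arms** (constant hazards).

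- Equal mortality of 25%, r of 5% versus 10%: cumulative incidences are 4.35% and 8.71%, a ratio of 2.00, as with Kaplan-Meier.
- Same reoperation hazard (r = 10% in both arms), assumed mortality 20% versus 30%: Kaplan-Meier gives 10% in both arms, while the proportions actually reoperated are 9.0% and 8.4%.

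**The case against.** **Censoring at death is inferred, not written.** The sentence names two endpoints and says nothing about how deaths are handled. If reoperation and death formed one composite endpoint, this bias would not arise, and the mortality curve is unaffected in any case. That stands as a caveat. But the plural endpoints, and the definition of failure as reoperation alone, point to two curves. A composite would also not give an implant failure rate. The choice of Kaplan-Meier for reoperation is stated in the article, so it is not merely a detail left to a fuller document.

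**The effect is small against sampling error.** With 100 patients per group, the 95% half-width around a 5% risk is 1.96 × √(0.05 × 0.95/100) = 4.3 points, against an excess of 0.7–0.8 points under constant hazards. Reoperation is not named among the primary or secondary outcomes, and it does not drive the sample size. This stands and limits the weight of the point, although the error is systematic and runs in one direction.

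**Net implant failure is a legitimate quantity.** The article itself cites long-term stem survival for the cemented prosthesis. This is also fair, but a net risk should then be labelled as such and not presented as the proportion of patients reoperated.

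**What a reader might infer but the documents do not support.** One might conclude that a mortality difference would produce a spurious difference between the reoperation curves. Under independent hazards it does not: mortality does not enter 1 − exp(−h), so equal reoperation hazards give equal curves. The risk is the reverse, that a difference in actual risk stays hidden. One might also take 15–20% as the size of the bias. That figure needs a roughly constant reoperation hazard, which the article does not state.

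**Conclusion.** The point holds on the reading that reoperation and death are separate endpoints. With deaths censored, one minus Kaplan-Meier is never below the cumulative incidence, and exceeds it whenever deaths precede some reoperations. At the mortality the plan expects, the difference is worth correcting. Its size cannot be fixed from the article: the ranges in the tables rest on assumed reoperation risks and timings and on independent hazards, and only the mortality figures come from the plan.

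The fault lies mainly in the absolute one-year risk reported for each implant. With equal mortality the ratio between arms is essentially unchanged, and a comparison of cause-specific hazards with deaths censored is valid in either case. If mortality differs by arm, the difference in absolute risk is also misstated. This is a secondary analysis, so the point should be corrected before the analysis but does not threaten the main results.

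**What to change.** In the paragraph on survival analysis:

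- State that reoperation and death are analysed as separate endpoints.
- Estimate reoperation by the cumulative incidence function (Aalen-Johansen) with death as a competing event, and report the one-year difference between arms with a 95% CI.
- Compare the arms by the cause-specific hazard of reoperation.
- Keep Kaplan-Meier for mortality.

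The cost is one or two sentences, a little more analysis work, and possibly software other than SPSS, which the plan names for all analyses. Dates of reoperation and death are needed for the planned curves anyway, so no new data have to be collected.
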